## Methods

### Study Design

This 12-month, 2-arm, stratified randomized clinical trial will use purposive sampling. A total of 248 Black survivors with CaP will be allocated in a 1:1 ratio to one of two study arms: (1) The SAFE-CaPS arm (n=124) where participants will receive access to the SAFE-CaPS app in addition to SC; or (2) Control arm (n=124) where participants will receive SC as recommended by their oncologist or other health care provider. SC will vary across participants and may include provider visits, referrals to specialists as indicated, and opportunities to receive support as needed. A stratified randomization approach will ensure a balanced representation of participants across diverse ethnic backgrounds. This study was reviewed and funded by the Department of Defense Prostate Cancer Research Program under Award Number HT942525PCRPIDA (Multimedia Appendix 1). This protocol was developed in accordance with the SPIRIT (Standard Protocol Items: Recommendations for Interventional Trials) 2025 guideline [51]. The completed SPIRIT checklist is included in Multimedia Appendix 2.

### Inclusion and Exclusion Criteria

Participants will be eligible if they (1) self-identify as Black, including native-born Black men, Caribbean-born Black men, and African-born Black men; (2) have a self-reported confirmed diagnosis of CaP within the last 5 years; (3) are between the ages of 40 and 80; and (4) own or will use a smartphone (Android or iOS).

Participants will be excluded if they do not meet the eligibility criteria listed above or if they are (1) unable or unwilling to provide a valid Social Security Number or Individual Taxpayer Identification Number, or do not meet U.S. residency requirements needed to comply with university reporting and compensation policies; or (2) currently enrolled in another structured CaP survivorship or support program.

### Study Recruitment and Procedure

Using purposive and snowball sampling, participants will be recruited through multiple channels across the United States via our current registries (more than 250 registered survivors with CaP), community-based approaches including our Community Advisory Board [52] members [30], fraternities, and the Inclusive Cancer Care Research Equity [48] for Black Men Consortium [53] and other existing research networks and clinics. The goal is to enroll a diverse population of Black survivors with CaP who meet the study criteria.

The first recruitment strategy will involve active collaboration with 1 of the co-investigators (medical oncologist), allowing recruitment through the urologic cancer clinics at the OU Health Stephenson Cancer Center (SCC). Clinical staff will identify eligible patients and assist with data collection during clinic visits. The second recruitment strategy will leverage the Clinical Research Data Warehouse at the SCC, enabling targeted recruitment. An electronic medical record data pull will identify potentially eligible participants. Identified participants will be contacted via mail and or phone. The third strategy will use existing research networks in Florida and Georgia, as well as a database of 108 Black survivors with CaP maintained by the senior author (MO). National social media recruitment will be conducted via ResearchMatch [54], a national health volunteer registry, in collaboration with an in-house marketing team to promote study participation through digital channels. Finally, community-based recruitment will be implemented through partnerships with the SCC Community Outreach and Engagement Core, the SCC African American Cancer Research CAB, and established community relationships, including faith-based organizations, the Prostate Cancer Survivorship CAB [30], the Inclusive Cancer Care Research Equity for Black Men Consortium [53], and the Mayo Clinic Minority Health & Health Equity Research Support initiatives [55]. Community education events will serve as engagement opportunities to enhance recruitment. A 1-page QR code-embedded recruitment flyer containing study details, eligibility criteria, and the study phone number will be distributed at community organizations, churches, and barbershops frequented by Black men. The multipronged recruitment strategy outlined has been successfully used in Black communities and is designed to address potential reluctance to participate in clinical trials [56,57]. Interested individuals will complete an online screening form or call the study phone number.

Participants in the SAFE-CaPS intervention group who do not own a smartphone will be provided with an Android smartphone and basic cell phone service to ensure equitable access. Those who already own an Android or Apple smartphone will use their personal device. All participants randomized to the intervention will receive a unique, single-use code to download the Insight app developed by the SCC mHealth Technology Shared Resource [58]. Upon entering the code, they will complete the baseline assessment and have access to the app for a 12-month period. Participants will receive practical instructions on using the app from the research team and there will be an option for a video tutorial outlining the features, and a video tutorial outlining the app's features will be available during the initial visit. This tutorial video can be saved to the phone's home screen for future reference, if needed by the participants. Participants will also be instructed on how to exclude the Insight app from “Do Not Disturb” mode settings on Android and Apple devices to ensure that ecological momentary assessments (EMAs) are received and completed in a timely manner. This guidance aims to reduce missed notifications due to phone settings and enhance EMA completion rates. The Insight app will serve as the platform for assessment and intervention for study groups. During the baseline assessment, participants will receive instructions on app features and complete prompted EMAs. These instructions are also available on demand via the “App Instructions” button on the app's home screen. Participants will complete a weekly, app-prompted EMA throughout the study. The app will also prompt participants to complete follow-up surveys at months 3,6, 9, and 12. Additionally, a subset of participants in the intervention group (n=30) will be invited to schedule an exit qualitative interview with a research team member to gather feedback on their experiences using the app.

Participants in the control arm will receive SC as directed by their oncology providers, which may include clinic visits, specialist referrals, or support services. No additional educational materials, digital tools, or support will be provided by the study team beyond the scheduled assessments. They will not have access to the Insight app or EMAs. Participants in the control group will complete baseline and follow-up surveys through a secure REDCap (Research Electronic Data Capture; Vanderbilt University) link [59]. QoL assessments will be completed via REDCap at months 3, 6, 9, and 12. The planned flow of participants through screening, enrollment, randomization, intervention, and follow-up assessments is presented in Figure 1.

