### Intervention (SAFE-CaPS)

The SAFE-CaPS intervention is designed to provide real-time symptom monitoring and management of CaP-related symptoms while integrating culturally relevant content and psychosocial support. Acknowledging the importance of emotional well-being, the intervention includes resources for mental health support to improve coping with psychological challenges related to CaP survivorship.

The development of the SAFE-CaPS app was guided by a Community-Based Participatory Research approach, ensuring that the needs and lived experiences of Black men with CaP shaped its design and implementation [8,9,29,30]. The intervention is built upon findings from our prior work exploring QoL among ethnically diverse Black men with CaP [8,9,29]. This research identified key survivorship concerns, including symptom burden, psychosocial distress, and unmet informational needs, highlighting the necessity of a culturally responsive intervention. To increase relevance and usability, the app underwent iterative refinement in collaboration with a CAB composed of ethnically diverse Black men survivors with CaP [30]. Through focus groups, usability testing, and feedback from Black men experiencing CaP survivorship, the app was tailored to reflect their preferences, values, and health care experiences. Unique features include culturally relevant health education and an emphasis on peer support and interactions with trusted health care providers. Additionally, the intervention addresses historical health care mistrust by integrating educational modules that empower users to navigate the health care system and communicate effectively with providers.

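### Eligibility does not exclude men who helped develop or test SAFE-CaPS, although recruitment runs through what appears to be the same advisory board; the main exposure is in the app-arm-only outcomes

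*Protocol article*

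**What the plan says.** **Recruitment.** Study Recruitment and Procedure uses purposive and snowball sampling. It lists "community-based approaches including our Community Advisory Board [52] members [30], fraternities" among the channels and also recruits "via our current registries (more than 250 registered survivors with CaP"). The same section later names "the Prostate Cancer Survivorship CAB [30]" as a community partner and mentions a database of 108 survivors held by the senior author.

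**Development.** Intervention (SAFE-CaPS) reports that "the app underwent iterative refinement in collaboration with a CAB composed of ethnically diverse Black men survivors with CaP [30]". It continues: "Through focus groups, usability testing, and feedback from Black men experiencing CaP survivorship, the app was tailored to reflect their preferences".

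**Eligibility.** Inclusion and Exclusion Criteria requires self-identification as Black, a diagnosis within 5 years, age 40 to 80, and a smartphone owned or accepted. Beyond failing these, there are two grounds for exclusion. One is being "unable or unwilling to provide a valid Social Security Number or Individual Taxpayer Identification Number" or not meeting residency requirements. The other is being "currently enrolled in another structured CaP survivorship or support program".

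**Separation of arms.** Controls have no access to the app or its momentary assessments during the trial. Exposure before randomisation is not mentioned. Randomisation is stratified by ethnic background only.

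**The concern.** The authors guard against men who are in a competing programme, but not against men who have already worked with the intervention under test. A man who sat on the refining board, joined a focus group or tested the app can satisfy every written criterion.

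Two consequences follow if such men enter.

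- **In the app arm**, they would use and rate a product they helped shape. Engagement, usability, the technology-acceptance survey and the exit interviews exist only in this arm. Randomisation therefore supplies no control group against which favourable ratings would cancel. The abstract's conclusions name feasibility and acceptability among what the trial will show, so these results carry weight.
- **In the control arm**, they might already know some of the self-management content. That would shrink the difference in FACT-P between arms.

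**Working it through.** **Step 1: can the men enter?** Setting the sections side by side:

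| Question | Section | Answer |
|---|---|---|
| Is a survivorship advisory board a recruitment channel? | Study Recruitment and Procedure | Yes, with citation 30, in two places |
| Did a board of survivors refine the app? | Intervention (SAFE-CaPS) | Yes, with citation 30 |
| Were other survivors exposed in development? | Intervention (SAFE-CaPS) | Yes: focus groups, usability testing, feedback; numbers not given |
| Does any criterion exclude them? | Inclusion and Exclusion Criteria | No |
| Is prior exposure a stratification factor? | Study Randomization | No |

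The residency and tax-number exclusion has no bearing on exposure. The programme exclusion concerns current enrolment in another programme, so past work on this one falls outside it. The age limits and the 5-year window would remove some board members and testers, but not all by construction.

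**Step 2: reproduce the plan's sample size.** Inputs from Sample Size and Power Analysis: standardised effect 0.39, alpha 0.05, power 80%, 1:1 allocation, 15% attrition. Two-sided testing is assumed because it reproduces the figure.

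- The two-sample t test needs 104.18 per group, rounded up to 105, as stated.
- 105 / (1 − 0.15) = 123.5, rounded up to 124 per group and 248 in total, as stated.
- Power at 105 per group with d = 0.39 is 80.3%.

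**Step 3: dilution of the FACT-P contrast.** Let f be the share of controls exposed beforehand and r the share of the benefit they keep. Then d = 0.39 × (1 − f × r). Neither f nor r is in the documents, so both are assumptions.

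| f | r | d | Power at 105 per group |
|---|---|---|---|
| 0 | – | 0.390 | 80.3% |
| 2% | 0.5 | 0.39 × 0.990 = 0.386 | 79.5% |
| 5% | 0.5 | 0.39 × 0.975 = 0.380 | 78.3% |

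As head counts, 2% of 124 controls is 2.5 men and 5% is 6.2 men. With an even split between arms, that means about 5 to 12 exposed men among the 248.

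**Step 4: app-arm outcomes.** No comparable calculation is possible. These outcomes have no control group, and the number of exposed men is unknown. The concern here is the direction of bias, which would be favourable.

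**The case against.** **The board is a route to participants, not a pool of them.** The text places it beside faith-based organisations and a consortium, and nowhere says that its members will be enrolled. This stands. A reader might infer that the trial plans to randomise its own co-designers, and the document does not support that. It supports only that nothing written prevents it.

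**One board or two?** The identity rests on the shared citation 30. The first mention also carries citation 52, and a second advisory board, with no stated link to app development, is among the partners. A single board is the likely reading but remains an inference. The gap does not depend on it, because focus-group participants and testers are equally uncovered. Whether such men are also in the registries or the 108-man database is not stated.

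**The article is condensed.** A fuller protocol or the online screening form might contain the exclusion. That is possible, and the sponsor could then simply confirm it. However, the article sets out its eligibility criteria as a list and does address a neighbouring form of contamination, so the point is worth raising.

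**Harm to the primary outcome could be overstated.** One could suppose that 10% of controls were exposed and kept the whole benefit, which would bring power to about 72%. The documents do not support this. The active parts of the intervention (daily assessments, symptom alerts, adaptive education and contact within 24 hours) need live access, which controls lack. It would also imply about 12 exposed controls and about 25 exposed men overall, for which there is no evidence. Randomisation balances prior exposure in expectation, and dilution moves the estimate toward zero, so it cannot create a false positive on FACT-P.

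**The app-arm outcomes are secondary and the interviews are analysed thematically.** Both are true. No between-arm inference is affected, and a share of interviewees is not a bias estimate. The descriptive acceptability findings would still be coloured by men with a stake in the product.

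**Conclusion.** The point holds as a gap in eligibility. As written, men who helped develop or test SAFE-CaPS can be randomised to either arm if they meet the age and diagnosis limits. The principal risk is favourable bias in results that only the app arm provides; its size cannot be computed. For FACT-P the loss is probably about 1 to 2 points of power (80.3% to between 79.5% and 78.3%), assuming that 2% to 5% of controls were exposed and kept half the benefit. The plan's sample size reproduces and needs no change. Since neither the number exposed nor the depth of their exposure is given, this is an inexpensive improvement to recommend. It is not a demonstrated flaw in the trial.

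**What to change.** - **Add one exclusion** to Inclusion and Exclusion Criteria: prior participation in SAFE-CaPS development (advisory-board refinement, focus groups or usability testing) or prior access to the app.
- **Verify it** with one screening question and a check against the development-phase lists.
- **State that advisory-board members act as referral sources only.** If the full protocol already says this, confirming it is enough.
- **Ask the men already enrolled** (6 at the time of the article). If any were exposed, keep them in the main analysis, report a sensitivity analysis without them, and leave them out of the exit-interview sample of 30.

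The target of 248 is unchanged. The cost is one amendment, one screening item and the loss of a few otherwise eligible men. It is lowest now, with 6 of 248 enrolled.

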**Methods:**

This 12-month stratified randomized clinical trial will enroll 248 Black survivors with CaP (including native born, African-born, and Caribbean-born men) into the SAFE-CaPS intervention arm and standard care (SC) control group (1:1 allocation). Eligible participants are self-identified Black men (including native born, African-born, and Caribbean-born) aged 40 to 80 years with a confirmed CaP diagnosis within the past 5 years who own or are willing to use a smartphone. SC will consist solely of routine oncology or primary care follow-up, including clinic visits, referrals, and supportive services as needed, with no digital components. The SAFE-CaPS intervention, developed using the Insight platform, includes daily and weekly ecological momentary assessments of pain, urinary and bowel symptoms, sleep, fatigue, sexual function, mood, physical activity, and diet; adaptive educational modules addressing treatment-related side effects and culturally grounded survivorship concerns; automated symptom alerts prompting nurse follow-up and provider notification; and engagement features such as reminders, goal-setting, and literacy-appropriate content. Intervention content incorporates culturally tailored messaging, patient narratives, and feedback from prior qualitative work with ethnically diverse Black CaP. Stratified randomization will ensure balanced representation of ethnic subgroups. Primary outcomes include overall QoL. Secondary outcomes include specific symptom domains, mental health (depression and anxiety), health care engagement, and app acceptability. Assessments will occur at baseline, 3, 6, 9, and 12 months, and linear mixed models with intent-to-treat principles will evaluate intervention effects over time.

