### Data Collection

Assessments will be conducted at baseline, post intervention, and interim time points at 3, 6, and 9 months. The assessment schedule is outlined in Table 1 (details of the assessment measures are provided in the Multimedia Appendix 3).

**Table 1 table1:** Overview of the questionnaire assessments.

EMA^a^ measures		Baseline (week 1)	Assessments (week 1-12)	Follow-up

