#### Primary Outcome

The primary outcome will be QoL, which will be assessed using the (FACT-P) questionnaire [72] at baseline, 3, 6, 9, and 12 months. FACT-P is a 39-item instrument that evaluates physical, emotional, and functional well-being, as well as CaP-specific concerns such as weight loss, appetite, pain, urinary symptoms, bowel function, and sexual health. Scores will be transformed onto a 0-100 scale, with higher scores indicating better QoL.

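### Baseline FACT-P in the SAFE-CaPS arm comes after randomisation and app activation, so it can be influenced by allocation and risks uneven missing data

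*Protocol article*

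**What the plan says.** Study Recruitment and Procedure gives the SAFE-CaPS order in consecutive sentences. The code goes to men whose allocation is already made: "All participants randomized to the intervention will receive a unique, single-use code to download the Insight app". Baseline comes next: "Upon entering the code, they will complete the baseline assessment and have access to the app for a 12-month period". App training is part of the same session: "During the baseline assessment, participants will receive instructions on app features and complete prompted EMAs". The app also prompts this arm's surveys at months 3, 6, 9 and 12.

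For the other arm the section names a different channel: "Participants in the control group will complete baseline and follow-up surveys through a secure REDCap" link. It does not say whether this happens before or after randomisation. The flow sentence lists no baseline step ahead of randomisation: "The planned flow of participants through screening, enrollment, randomization, intervention, and follow-up assessments is presented in Figure 1". Figure 1 itself is not available here.

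Primary Outcome makes FACT-P a baseline measure: "The primary outcome will be QoL, which will be assessed using the (FACT-P) questionnaire [72] at baseline, 3, 6, 9, and 12 months". Table 1 places baseline in week 1, the same week in which the week 1-12 assessments start. Study Randomization says that participants cannot be blinded. The Abstract states the analysis principle: "linear mixed models with intent-to-treat principles will evaluate intervention effects over time".

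**The concern.** A baseline value is a safe reference because allocation cannot have affected it. Here, a SAFE-CaPS man rates his own quality of life knowing that he has been given the app, and while he is being shown how to use it. His answers may rise with optimism or fall because the onboarding draws attention to symptoms. The Abstract plans an analysis over time, and the hypothesis is framed as greater improvement. If baseline enters the model as the reference, a shift in it passes into the treatment estimate, and it cannot be re-measured later.

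The second risk is missing data. Entering the code is an extra step that only SAFE-CaPS men face before they can give a first FACT-P, and their later surveys are prompted through the same app. Men who never activate may be less well or less comfortable with technology. If they provide no FACT-P at all, they contribute nothing to a mixed model, even one labelled intent-to-treat. Strengths and Limitations foresees differential loss only in the opposite direction, with more in usual care.

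**Working it through.** **Order of events.** In the SAFE-CaPS arm the sequence is stated: randomise, issue code, enter code, complete baseline during app instruction. In the control arm only the channel is stated (REDCap). Because the channel depends on the arm, allocation is probably known by then, but that is an inference.

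**The plan's own figures.** Inputs from Sample Size and Power Analysis: standardised effect 0.39, alpha 0.05 (taken as two-sided), 80% power, 1:1, attrition 15%.
- A two-sample t test needs 104.18 per group, rounded up to 105. This matches the plan.
- 105 / (1 - 0.15) = 123.5, rounded up to 124. This matches the plan.

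Nothing below changes these figures.

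**Effect of a shifted baseline.** Assumption: knowing the allocation shifts mean baseline FACT-P in one arm by s = 0.10 SD, and the shift does not persist to month 12.
- Change score, or a mixed model whose group-by-time contrast is measured from an unconstrained baseline: bias = s = 0.10 SD; 0.10 / 0.39 = 26%.
- Baseline-adjusted estimate: bias = r x s, where r is the baseline to 12-month correlation (assumed 0.5 to 0.7). 0.5 x 0.10 = 0.05 SD (13% of 0.39); 0.7 x 0.10 = 0.07 SD (18%).
- Unadjusted 12-month contrast: bias = 0.

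The sign depends on the cause. A raised SAFE-CaPS baseline works against the app, as does a control baseline lowered by disappointment. A lowered SAFE-CaPS baseline works in its favour.

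**Effect of losing non-activators.** Assumption: a share a of the SAFE-CaPS arm never activates, provides no FACT-P, and would have scored g SD lower. The full-arm mean is the activators' mean minus a x g, so analysing activators alone gives a bias of a x g in favour of the app. Type I error uses 124 x 0.85 = 105.4 controls and 124 x (1 - a) x 0.85 SAFE-CaPS men.

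| a | g | bias (SD) | share of 0.39 | two-sided type I error |
|---|---|---|---|---|
| 10% | 0.2 | 0.02 | 5% | 0.052 |
| 10% | 0.5 | 0.05 | 13% | 0.064 |
| 20% | 0.2 | 0.04 | 10% | 0.059 |
| 20% | 0.5 | 0.10 | 26% | 0.105 |

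Power at 0.39 under the same loss falls from 80.5% (none lost) to 78.3% (10%) and 75.7% (20%). The bias matters more than the loss of power.

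**The case against.** The strongest reply is that the planned primary comparison may not use baseline at all. The sample size rests on the 12-month difference. Analytic Plan models FACT-P at 12 months, and its open-ended covariate list does not name baseline FACT-P. No section specifies a change-score analysis. This stands: the 26% figure is conditional, and a plain 12-month contrast escapes the baseline problem. It does not dispose of the point, because the Abstract promises mixed models over time and the hypothesis concerns improvement.

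Three stronger readings are tempting, and the article does not support them.

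- A reader might infer that every man knows his arm at baseline. For controls this is implied by the arm-specific route but not stated. Figure 1 and Multimedia Appendix 3, which might settle it, are not available.
- A reader might infer that non-activators are dropped, and from one arm only. No section withdraws or excludes them, and a control who never opens the REDCap link would also lack a baseline. The real asymmetry is one additional step in one arm, and the study eases it with provided phones, instruction and a tutorial.
- A reader might infer that the intent-to-treat claim fails. The Abstract states that principle, and the app is said to prompt the follow-up surveys, not to be their only route. SAFE-CaPS men already use REDCap for the survey at 12 months (Post Intervention Survey). The fair statement is a risk of differential missing data. Strengths and Limitations does plan to monitor retention by arm.

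None of this alters the stated SAFE-CaPS sequence. If Figure 1 shows baseline before randomisation, then the recruitment text contradicts it and still needs correcting.

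**Conclusion.** The concern holds in limited form. As written, SAFE-CaPS men complete baseline FACT-P after randomisation and app activation, during onboarding, and by a different route from controls. With unblinded participants and a self-reported outcome, baseline in at least that arm can be influenced by allocation. That would bias an over-time, change-from-baseline or baseline-adjusted analysis, in either direction. The activation step, together with app-prompted follow-up, adds a risk of differential missing FACT-P data.

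The sizes are illustrative, since the article gives no baseline shift, non-activation rate or prognostic gap. A 0.10 SD shift costs 0.05 to 0.10 SD (13% to 26% of 0.39), depending on how baseline is used. Non-activation of 10% to 20% with a gap of 0.2 to 0.5 SD costs 0.02 to 0.10 SD (5% to 26%). The 105 and 124 per group are unaffected.

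**What to change.** State one order for both arms:

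1. Consent, the sociodemographic and clinical forms, FACT-P and PHQ-4 are completed in REDCap by every participant before the randomisation module is opened.
2. The app code is issued, and app instruction given, only afterwards.
3. SAFE-CaPS men who do not activate the app receive each follow-up FACT-P by REDCap link, so that they stay in the intent-to-treat analysis.

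Check Figure 1 and Table 1 against this order and correct whichever disagrees.

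The cost is small. REDCap already hosts the control surveys and the randomisation module, so the change is a reordering of forms, a follow-up link and a short amendment. The downside is that participants enrolled before the change have a differently timed baseline and should be flagged in the data. Results reports 6 at the time of writing, which would leave 248 - 6 = 242; recruitment was open, so the current count may be higher.

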### Study Randomization

This study will use a 1:1 stratified randomized controlled trial design and will enroll 248 participants who will be randomly assigned to either the SAFE-CaPS intervention group (n=124) or the control group (n=124) using REDCap’s stratified randomization module. Stratification will be based on ethnic background to ensure a balanced representation across study arms: native-born Black men (n=100), African-born Black men (n=74), and Caribbean-born Black men (n=74). Within each subgroup, participants will be randomized in equal numbers to the intervention and control arms (native-born Black men: 50/50; African-born Black men: 37/37; Caribbean-born Black men: 37/37). This stratified approach ensures balanced subgroup representation and supports exploratory analyses assessing potential differences in survivorship experiences and intervention response across ethnic backgrounds.

Due to the nature of the intervention, blinding of participants, care providers, and recruitment staff is not feasible. However, the data analyst will be blinded to group allocation to reduce analysis bias.

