#### Post Intervention Survey

Twelve months post-randomization, participants assigned to SAFE-CaPS will complete a structured online survey via REDCap to assess intervention engagement, usability, and changes in health behavior, based on the UTAUT framework. The survey will evaluate participants' responses to the 4 key intervention constructs: performance expectancy, effort expectancy, social influence, and facilitating conditions, along with their final behavioral intent.

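### FACT-P appears to be prompted and collected by the Insight app in the SAFE-CaPS arm and by a REDCap link in the control arm; use one route for both

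*Protocol article*

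**What the plan says.** All references are to the Methods of the protocol article.

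- **SAFE-CaPS arm (Study Recruitment and Procedure).** Men randomized to the intervention receive a code for the app. Then: "Upon entering the code, they will complete the baseline assessment and have access to the app for a 12-month period". The same paragraph adds: "The Insight app will serve as the platform for assessment and intervention for study groups". On follow-up: "The app will also prompt participants to complete follow-up surveys at months 3,6, 9, and 12".
- **Control arm (same section, next paragraph).** "They will not have access to the Insight app or EMAs". The route for this arm is explicit: "Participants in the control group will complete baseline and follow-up surveys through a secure REDCap" link. The following sentence names no arm: "QoL assessments will be completed via REDCap at months 3, 6, 9, and 12".
- **REDCap in the SAFE-CaPS arm (Post Intervention Survey).** At month 12, "participants assigned to SAFE-CaPS will complete a structured online survey via REDCap to assess intervention engagement, usability, and changes in health behavior". No other section names REDCap explicitly as a survey route for this arm.
- **Table 1.** FACT-P and PHQ-4 are listed in a table whose measures column is headed as EMA measures.
- **Primary Outcome.** FACT-P is measured at baseline and at the four quarterly visits.
- **Study Randomization.** Participants, care providers and recruitment staff are not blinded, but "the data analyst will be blinded to group allocation to reduce analysis bias".

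**The concern.** FACT-P is a subjective score given by men who know their arm. If one arm answers inside the app being evaluated, after app notifications, and the other answers from a survey link, then mode, prompting and response setting coincide with treatment. The 12-month contrast would estimate the intervention effect plus any effect of these, and nothing within either arm allows them to be told apart. A man who stops using the app may also be harder to reach for his outcome, and controls have no counterpart to this.

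Two further points follow. The wording on the assessment platform cannot be reconciled with a control arm that is denied the app. And if FACT-P arrives from two systems, the source of a record shows its arm unless someone removes that information before the blinded analyst sees it.

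**Working it through.** **1. Which route does the text give?**

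| Item | SAFE-CaPS | Control |
|---|---|---|
| Baseline | Completed on entering the app code | REDCap link |
| Follow-up surveys | Prompted by the app | REDCap link |
| App access | Yes | None |
| REDCap named | Month-12 technology-acceptance survey | All surveys |

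Three statements favor in-app entry for SAFE-CaPS: baseline follows the app code, the app is called the assessment platform, and Table 1 places FACT-P among the EMA measures. Two leave the matter open: a prompt is not a place of entry, and the REDCap sentence on QoL names no arm. In-app entry is therefore the natural reading, but an inference. Prompting by the app in one arm only is stated.

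**2. The plan's own figure** (Sample Size and Power Analysis: effect 0.39 SD, alpha 0.05, power 80%, 1:1, attrition 15%).

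- Normal approximation, two-sided: n = 2 × (1.960 + 0.842)² / 0.39² = 103.2, so 104 per group. The two-sample t test gives 104.18, so 105, as stated.
- With attrition: 105 / 0.85 = 123.5, so 124 per group and 248 in total, as stated.

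The sample size reproduces and is not in question.

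**3. What a shift in one arm would do.** The documents give no size, so a range is assumed. With 105 per arm, SE = √(2/105) = 0.138 SD. For a shift b:

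- share of the design effect = b / 0.39
- false-positive rate with no true effect = P(|Z + b/SE| > 1.96)
- power if the shift goes against the app = Φ((0.39 − b)/SE − 1.96)

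| Shift (SD) | Share of 0.39 | False-positive rate | Power if against the app |
|---|---|---|---|
| 0 | 0% | 5.0% | 80.7% |
| 0.05 | 13% | 6.5% | 69.3% |
| 0.10 | 26% | 11.2% | 55.6% |
| 0.15 | 38% | 19.3% | 41.3% |
| 0.20 | 51% | 30.5% | 28.0% |

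These figures are for the unadjusted 12-month comparison used for sizing.

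**4. Unequal loss.** Keep the average loss at 15% but split it 10%/20% or 5%/25% between the arms. Power is 80.7% or 80.3%, almost unchanged. If the men lost differ from their arm's mean by 0.25 to 1 SD, the difference between completers moves by (difference in loss) × (that gap):

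- 10%/20%: 0.10 × 0.25 to 0.10 × 1 = 0.025 to 0.10 SD
- 5%/25%: 0.20 × 0.25 to 0.20 × 1 = 0.05 to 0.20 SD

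The sign depends on which arm loses more and on whether the men lost score lower or higher. The issue is bias, not precision.

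**The case against.** The strongest reply is that the article does not say SAFE-CaPS men enter FACT-P in the app. A notification that opens a REDCap form fits the text, and these men do use REDCap at month 12. Both routes are also self-completed electronic questionnaires, so a large mode effect is not evident. This stands, and it is why the point is put conditionally. It does not remove the contradiction over the platform or the one-sided prompting.

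A constant mode shift would also be present at baseline and could be partly removed by baseline adjustment. That requires the shift to be constant, and it would not deal with prompting or non-response. Baseline FACT-P is not among the covariates named in the Analytic Plan.

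A reader might draw three stronger conclusions that the documents do not support:

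- **Analyst blinding is undone.** Someone else can merge two sources under masked arm codes. Survey source is not even the clearest threat. The Analytic Plan covers app usage, which exists in one arm only. Study Compensation makes total payment a sensitivity covariate, and any total above the control maximum of US $175 identifies a SAFE-CaPS man (maximum US $685 or US $735).
- **Missing data will flatter the app.** Nothing says that muting or deleting the app ends outcome collection, or that disengaged men score lower. Strengths and Limitations expects more loss in the control arm, because of motivation and payment, and plans to monitor retention by arm.
- **FACT-P is lost once app access ends at 12 weeks.** The 12-week access in Daily EMAs conflicts with the 12 months given under recruitment. Yet Daily EMAs itself schedules assessments after the 6-, 9- and 12-month visits. That inconsistency is separate and needs its own reconciliation.

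**Conclusion.** The point holds in a limited form. The article contradicts itself on the assessment platform, states app prompting for one arm only, and on its natural reading collects an unblinded, self-reported primary outcome by different systems in the two arms. If so, mode and prompting coincide with arm, and response in one arm depends on continued use of the product under test. Direction and size are unknown. The range of 0.05 to 0.20 SD, or 13% to 51% of the design effect, is an assumption that shows what would matter and is not an estimate. Analyst blinding is at risk until masking is arranged. No sample-size figure changes. The change is worth making because it is cheap and removes a confounder that the analysis could not reliably correct.

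**What to change.** 1. Reconcile the intervention and control paragraphs of Study Recruitment and Procedure, and state the FACT-P route for each arm.
2. Collect FACT-P and PHQ-4 at all five time points through the same REDCap form in both arms, with the same reminder schedule and wording. Keep the app for EMAs and intervention content.
3. Record the collection route for the men already enrolled.
4. Until the primary analysis is locked, give the analyst only a coded-arm FACT-P and PHQ-4 file plus the baseline covariates, without platform, EMA-usage or compensation fields.

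**Cost.** Small. REDCap already runs in both arms and handles randomization, and only 6 of 248 men are enrolled, 2 of them in SAFE-CaPS. SAFE-CaPS men would use a second interface about five times in the year, and the few already enrolled may have mixed modes. One form does not make all contact equal: SAFE-CaPS men still receive EMA prompts and EMA payments. It does equalize how the primary outcome is requested and recorded.
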